**Sample restriction**		
PWOUD with chronic pain.	To evaluate treatment effect variability in populations prioritized by The American Society of Addiction Medicine national practice guidelines.[87]	Both
Adolescents.		Both
Individuals in the criminal justice system.		Both
PWOUD with mental health disorders. ^a^		Both
PWOUD with history of prescription opioid prior to OUD diagnosis.	To evaluate the robustness of treatment effects among individuals who primarily misuse PO.	Both
PWOUD in regions with highest fentanyl concentrations. ^b^	To understand the robustness of treatment effects in areas where illicit fentanyl use is most prevalent.	Both
PWOUD receiving care in Community Health Centres. ^c^	To evaluate heterogeneity of treatment association across clinical settings.	Both
PWOUD receiving care in stand-alone physician practices. ^d^		Both
Excluding PWOUD receiving OAT by primarily detox prescribers. ^e^	To evaluate the robustness of treatment effect by removing individuals receiving OAT for rapid detoxication.	Both
Excluding OAT episode initiating right after hospital discharge.	To evaluate the treatment association among OAT episodes with its first dose dispensed at community pharmacy.	Both
Excluding PWOUD with indication of heart failure or cardiomyopathy.	To remove individuals with pre-existing risk of prolonged QT interval, which is a caution for initiating methadone	Both

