### Adapting clinical guidelines to a new drug landscape

Clinical guidelines in BC had previously regarded SROM as a third-line treatment behind buprenorphine/naloxone and methadone but updated their guidance in 2023, in response to rising overdose death rates across the province, to remove the tiers and advise collaborative treatment selection based on client preferences, clinical judgement and contextual circumstances.[6] Guidance for SROM is largely based on clinical consensus and expert opinion due to overall limited evidence to support decision-making.[6] This client-centered shift acknowledges that prior experiences with OAT often shape future treatment decisions. SROM may be an alternative option for individuals who have experienced negative outcomes with other OAT medications, such as incomplete elimination of withdrawal with buprenorphine/naloxone, or intolerable side effects with methadone, including sedation, emotional blunting, or cardiac risks such as QT prolongation.[11] Individuals with contraindications to methadone, including ventricular arrhythmias or concurrent use of QT-prolonging medications, may particularly benefit from SROM as the medication does not affect the QT interval.[11] Moreover, frequent or early switching between OAT options is often a signal of suboptimal treatment fit, whether due to poor tolerability, inadequate therapeutic response, or individual treatment goals not being met.[6,11]

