### Covariate selection

We propose to include all selected confounders identified in a recent methadone versus buprenorphine/naloxone study,[61] which applied a modified disjunctive cause criterion[62] to the augmented list of covariates from systematic reviews.[63,64] These covariates include socio-demographic factors, measures of disease severity and comorbidity, and OAT-related factors. Additionally, COVID-19-related covariates will be included to control potential selection bias introduced by pandemic-related service disruptions and differential treatment accessibility (see Table 4 for the list of covariates).

All time-varying covariates will be updated weekly. These covariates will be used to estimate the inverse probability of treatment as well as censoring weights to adjust for measured confounding and informative censoring respectively.

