Prevalent new users with past OAT experience	(iii) A history of methadone dispensation within past year of the index OAT episode	To assess individuals with recent prior experience of specific OAT which may influence current treatment response.
	(iv) A history of buprenorphine/naloxone dispensation within past year of the index OAT episode	
	(v) A history of methadone and buprenorphine/naloxone dispensation in past two years of the index OAT episode	
Prevalent new users who had previously completed OAT induction*	(vi) Completed methadone induction within past two year of the index OAT episode	To assess individuals recently stabilized on methadone and buprenorphine/naloxone, which may influence response to new treatment.
	(vii) Completed buprenorphine/naloxone induction within past two year of the index OAT episode	
	(viii) Completed methadone and buprenorphine/naloxone induction in past five years of the index OAT episode	A history of completing both inductions may reflect complex needs or higher tolerance, informing comparative effectiveness.
Individuals initiated treatment with buprenorphine/naloxone	(ix) Individuals initiated OAT with buprenorphine/naloxone will be included. Switching to SROM within 30 days of initiation will be compared with staying on buprenorphine/naloxone in a two-arm study.	Early switching within buprenorphine/naloxone episode may indicate suboptimal response or poor tolerability.
Individuals initiated treatment with methadone	(x) Individuals initiated OAT with methadone will be included. Switching to SROM within 30 days of initiation will be compared with staying on methadone in a two-arm study.	Early switching within methadone episode likely reflects adverse effects such as sedation, emotional blunting, or QT-related cardiac risk.

* Induction completion is defined as no dose change within at least two consecutive weeks.

**Table 3. T3:** Censoring indication in the primary and secondary analyses for comparing slow-release oral morphine versus methadone and buprenorphine/naloxone.

	OAT discontinuation		All-cause mortality		Overdose-related acute-care visits	
	Initiator	Per protocol	Initiator	Per protocol	Initiator	Per protocol
OAT discontinuation	outcome	outcome				
End of study ^a^	C_1_	C_1_	C_1_	C_1_	C_1_	C_1_
Death	C_2_	C_2_	outcome	outcome	C_2_	C_2_
Loss to follow-up	C_2_	C_2_	C_2_	C_2_	C_2_	C_2_
Deviation from inclusion/exclusion criteria		C_2_		C_2_		C_2_
Deviation from the protocol		C_3_		C_3_		C_3_

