Severe mental disorder (ever)^‡, a^	Yes/No	Includes major depressive disorder, bipolar disorder, and schizophrenia, and identified through ICD codes if diagnosed ever and updated if diagnosed during episode follow-up.
Alcohol use disorder (ever)^‡, a^	Yes/No	Identified through ICD codes and DIN/PIN, if diagnosed ever and updated if diagnosed during episode follow-up.
Hepatitis C virus (ever) ^‡, a^	Yes/No	Identified through ICD codes if diagnosed ever and updated if diagnosed during episode follow-up.
Asthma (ever)^‡, a^	Yes/No	Identified through ICD codes* and DIN/PIN within the past year, updated during the follow-up.
Chronic pain in past year^‡, a^	Yes/No	Identified through ICD codes within the past year, updated during follow-up.
Chronic obstructive pulmonary disease^‡, a^	Yes/No	Identified through ICD codes within the past year, updated during the follow-up.
Charlson comorbidity index in past year^‡^	0 and above	Using the Charlson comorbidity index[66] and hospitalization records within the past year, and updated during the follow-up.
Dispensations of psychiatric or sedative medication in the past month^‡, a^	Yes/No	Identified through DIN/PIN of dispensations in the past 30. Updated during the follow-up.
*Factors related to OAT experience*		
Dispensations opioid other than OAT in the past month^‡, a^	Yes/No	Identified through DIN/PIN and a case-finding algorithm used prior[67] and updated during the follow-up.
Received prescription opioids other than OAT prior to OUD diagnosis ^a^	Yes/No	Identified through DIN/PIN and a case-finding algorithm used prior[67] and updated during the follow-up.
Treated tobacco use disorder in past year^‡, a^	Yes/No	Based on ICD-10 codes and indication of nicotine replacement therapy in PharmaNet
Attachment to the prescriber ^‡, a^	Yes/No	Identified based on billing history from the physician. More than 50% of physician billing attributed to the prescriber in the past 12 months
Funding of prescribers who initiated OAT: alternative payment plan	Yes/No	Alternative payment plan indicated by the absence of a medical services plan billing record (capturing fee-for-service billing) at initial OAT dispensation.
Urine drug test in the past week^‡^	Yes/No	Receipt of urine drug test from physician billing records
Practice size^‡^	Large, medium, small	Determined by network analysis; number of unique OAT clients in past 12months. Large for >300 clients, medium for 16–300 clients and small for ≤15 clients.
*COVID-19 related factors*		

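### The QT restriction in Table 5 leaves out the two methadone contraindications the protocol itself names, and Table 4 does not adjust for them

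*Protocol article*

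**What the plan says.** The Introduction (Adapting clinical guidelines to a new drug landscape) states: "Individuals with contraindications to methadone, including ventricular arrhythmias or concurrent use of QT-prolonging medications, may particularly benefit from SROM". The same section lists, among reasons for considering SROM, "intolerable side effects with methadone, including sedation, emotional blunting, or cardiac risks such as QT prolongation". For sub-population (x), methadone starters who do or do not switch to SROM within 30 days, Table 2 gives this rationale: "Early switching within methadone episode likely reflects adverse effects such as sedation, emotional blunting, or QT-related cardiac risk".

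The one analysis directed at QT risk is a sample restriction in Table 5, "Excluding PWOUD with indication of heart failure or cardiomyopathy", marked for both the initiator and the per-protocol framework. Its stated aim is: "To remove individuals with pre-existing risk of prolonged QT interval, which is a caution for initiating methadone".

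The adjustment set is in Table 4. Covariate selection explains its origin: "We propose to include all selected confounders identified in a recent methadone versus buprenorphine/naloxone study"; the only stated addition is a group of COVID-19 variables. The nearest items to QT risk are a comorbidity score, defined as "Using the Charlson comorbidity index[66] and hospitalization records within the past year, and updated during the follow-up", and a yes/no item for any psychiatric or sedative drug dispensed in the past month.

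The high-dimensional propensity score (hdPS) and instrumental variable (IV) analyses are sensitivity analyses of the initiator effect only (Statistical analysis; Table 5). Table 1 gives sub-populations (ix) and (x) a per-protocol analysis but no initiator analysis.

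**The concern.** The protocol identifies a reason why some people receive SROM rather than methadone, and says which patient characteristics mark it. A characteristic that steers treatment and may also raise mortality is a confounder of the SROM versus methadone mortality contrast. It should be adjusted for, or removed in the analysis meant to remove it. Here the restriction uses other cardiac conditions, and the adjustment set holds neither named marker.

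Two things are at stake. First, the main models rely on whatever correlated covariates they happen to contain. Secondly, a reader of the final report may take a stable estimate under the Table 5 restriction as evidence that QT-driven selection does not matter, although people with a recorded ventricular arrhythmia or on a QT-prolonging drug would still be in that sample.

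**Working it through.** **1. Figures in the document.** The protocol gives no sample size, event count or prevalence for any QT marker, so there is no figure to reproduce. The finding rests on comparing the passages; the arithmetic in step 4 is for scale only.

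**2. Where each marker appears.**

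| Marker | Named as QT-related reason against methadone | Main eligibility | Table 4 covariate | Table 5 QT restriction |
|---|---|---|---|---|
| Ventricular arrhythmia | Yes (Introduction) | Not excluded | No | Not excluded |
| Concurrent QT-prolonging drug | Yes (Introduction) | Not excluded | No (only any psychiatric or sedative drug) | Not excluded |
| Heart failure or cardiomyopathy | Only in Table 5 | Not excluded | No separate item | Excluded |

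**3. What reaches each analysis.**

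- *Initiator analysis, (i) to (viii):* Table 4 weights without the two markers. hdPS searches hospital and physician diagnosis codes and PharmaNet drug classes, so it could pick up related codes. This is not assured: it uses a six-month look-back, drops codes seen in fewer than 50 people and keeps the top 200 per outcome. IV also targets uncontrolled confounding, with SROM set against the two comparators combined.
- *Per-protocol analysis, (i) to (viii):* Table 4 weights only; no hdPS or IV.
- *Sub-population (x):* the clone-censor-weight analysis conditions on covariate history, which means Table 4; no hdPS or IV. The Table 5 restriction runs here too, but leaves both markers in. No planned analysis therefore addresses the named markers directly, in the population where Table 2 cites QT risk as a reason for the exposure.

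**4. Illustrative size.** For a binary uncontrolled factor and a true mortality ratio of 1, the apparent SROM versus methadone ratio is

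B = [1 + p1(R − 1)] / [1 + p0(R − 1)],

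where p1 and p0 are the prevalences of the marker among SROM and methadone initiators, and R is its mortality ratio. All three are assumptions; none comes from the document.

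| p1 / p0 | R = 1.5 | R = 2 | R = 3 |
|---|---|---|---|
| 2% / 1% | 1.005 | 1.010 | 1.020 |
| 5% / 1% | 1.020 | 1.040 | 1.078 |
| 5% / 2% | 1.015 | 1.029 | 1.058 |
| 10% / 2% | 1.040 | 1.078 | 1.154 |
| 15% / 5% | 1.049 | 1.095 | 1.182 |
| 20% / 5% | 1.073 | 1.143 | 1.273 |

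For example, 2%/1% with R = 1.5 gives 1.010/1.005 = 1.005; 10%/2% with R = 3 gives 1.20/1.04 = 1.154; and 20%/5% with R = 3 gives 1.40/1.10 = 1.273. If the marker is commoner among SROM users and raises mortality, the bias runs against SROM. The formula ignores any correlation with covariates already adjusted for; to the extent that those act as proxies, it overstates what remains.

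**The case against.** The strongest reply has five parts.

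- *Different groups.* Table 5 speaks of a caution for starting methadone, the Introduction of contraindications, and the Introduction's list is introduced as examples. The restriction may thus be narrower than it could be without contradicting anything. This stands in part: a reader might infer that the restriction removes the wrong people, and the text does not show that. But its stated aim is to remove pre-existing QT risk, and it leaves in the two QT markers that the protocol names.
- *Proxies.* The comorbidity score and psychiatric or sedative dispensing are updated weekly and enter both the treatment and censoring models. The drug list is held elsewhere, so its overlap with QT-prolonging drugs cannot be judged. A reader might infer that QT-driven selection remains in full in the contrast; the documents support only that it is not directly controlled.
- *Other safeguards.* hdPS and IV are real mitigation for the initiator effect, and the Discussion acknowledges residual confounding through a non-exhaustive list. Neither method reaches the per-protocol analyses or (x).
- *Unknown result and size.* A reader might infer that the restriction is bound to show no change. Nothing supports that prediction, because neither the overlap between heart failure and the two markers nor their prevalence is given. The size may be negligible. No bias is shown for discontinuation or for the buprenorphine/naloxone contrast.
- *Proportion.* QT risk is one of three reasons in Table 2 (x), and the restriction is one of eleven in Table 5. The covariates came from a formal selection criterion, but in a study of methadone versus buprenorphine/naloxone, where reasons specific to choosing SROM were not at issue.

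**Conclusion.** The point holds in a limited form. The QT restriction does not cover the two methadone contraindications that the protocol names, and the covariate list contains neither. QT-driven channelling from methadone to SROM is therefore not directly controlled in the main models, and in (x) no planned analysis addresses it directly. A stable estimate under the restriction could be read as more reassuring than it is.

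The size is unknown. The illustrative factor on the SROM versus methadone mortality ratio, about 1.005 to 1.27, runs from negligible to material. It depends wholly on assumed inputs and is offset to an unknown degree by proxy covariates. The case for change rests on the mismatch and the low cost of closing it, not on a demonstrated bias.

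**What to change.** 1. In Table 5, extend the QT restriction so that it excludes, besides heart failure and cardiomyopathy, people with a recorded ventricular arrhythmia or long-QT code and people dispensed a QT-prolonging drug around time zero. The drug list should leave out the study treatments themselves, since the protocol attributes QT prolongation to methadone.
2. In Table 4, add both markers: arrhythmia ever, and QT-prolonging drug in the past month, updated weekly. Do this at least for the SROM versus methadone contrast and for sub-population (x).
3. Report overlap and the weight distribution after adding them. If few people with arrhythmia start methadone, treatment probabilities may approach zero; where positivity is poor, rely on the restriction rather than on weighting.

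Cost: code lists and two covariates from the hospital, physician and PharmaNet data already linked. Study status and timeline says that no analysis has been run, so the change can still be pre-specified. The restricted sample will be smaller, possibly more than slightly if QT-prolonging drugs are common, which means wider intervals in that analysis.

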**Timeline restriction**		
Pre-COVID era (June 1, 2017-March 17, 2020)	To evaluate the impact of the COVID era (post-March 17, 2020) on our results, as pandemic-related changes in prescribing practices and treatment accessibility— such as increased take-home doses, expanded telehealth, and relaxed urine drug testing—may have influenced treatment retention and outcomes.	Both

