### Impact of COVID-19 on OAT policies and outcomes

The COVID-19 pandemic necessitated substantial changes in OAT delivery to ensure continued care while minimizing in-person interactions. Across multiple jurisdictions, including Canada,[34,35] the U.S.,[36,37] Australia,[38] New Zealand,[39] and the United Kingdom,[40] regulatory changes were implemented to expand take-home dosing, integrate telehealth consultations, and ease urine drug testing requirements. These policy shifts broadened OAT accessibility, particularly for individuals facing barriers to in-person daily treatment.[35] A survey-based study from Ontario involving 402 patients and 100 prescribers found that expanded unsupervised dosing during COVID-19 was not associated with increased rates of overdose, emergency department visits, or hospitalizations, although diversion behaviors such as dose sharing and trading were more frequently reported.[35] While these adaptations largely applied to methadone and buprenorphine/naloxone, the impact on SROM accessibility and treatment outcomes remains unclear.[34] Interviews with 25 opioid treatment program directors in the U.S. revealed mostly positive responses to COVID-related regulatory changes, though some raised concerns about reduced clinical oversight, medication diversion, and patient isolation.[41] Additionally, while 37 U.S. states initially adopted expanded methadone take-home flexibilities, four states later rescinded these changes, reverting to pre-pandemic regulations.[37] These findings highlight the variability in policy implementation across jurisdictions and raise questions about the long-term sustainability of these regulatory adaptations.

BC operates within a single-payer healthcare system where access to OAT is not restricted by site type or insurance status. Unlike the U.S., where OAT coverage often depends on Medicaid expansion and site-specific regulations (e.g., methadone often limited to certified clinics), BC allows OAT delivery in diverse clinical settings and provides a wider range of medications, including SROM. This unique regulatory landscape provides a rare opportunity to generate real-world evidence on SROM’s effectiveness relative to methadone and buprenorphine/naloxone using the population-based linked administrative dataset in BC.

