where $SW_{it}$ is the stabilized weight for the *i*th individual at time t, $C_{ij}$ is the censoring status for the *i*th individual at *j*th time, ${\bar{C}}_{ij}$ is the censoring history for the *i*th individual at *j*th time, $L_{i0}$ is the list of time-fixed covariates including treatment arm, ${\bar{L}}_{ij}$ is the time-dependent covariate history for the *i*th individual at *j*th time. Time-dependent covariates will be lagged by one week to ensure censoring is predicted using prior-week covariates. Same set of baseline and time-varying covariates will be included in the treatment and censoring models. Both treatment weights at time zero and censoring weights will be stabilized, truncated at the 99th percentile to limit the influence of extreme values and their product will be used as the final weights.[72] Covariate balance will be assessed using standardized mean differences (SMD), with SMD <0.10 considered balanced.[77] To fit the marginal structural model, a pooled weighted logistic regression model will be fitted to compare the time to OAT discontinuation, all-cause mortality, and overdose-related acute care visits across treatment groups. Based on the fitted models, individual time-to-event (survival) probabilities will be predicted weekly for each treatment arm by setting the treatment equal to a specific value (e.g., SROM, methadone, or buprenorphine/naloxone) for all individuals. These predicted probabilities will then be averaged across the population to get week-specific survival probabilities. The risk of the events will be estimated as one minus the averaged survival probability, with risk differences calculated for SROM initiators versus buprenorphine/naloxone and methadone. We will report hazard ratios, risk differences, and risk curves. Compatibility intervals and curves will be computed using the approach described in the Statistical analysis section.

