Virtual care^‡^	Yes/No	Virtual care indicated in physician billing records.[68,69]
OAT pharmacy delivery^‡^	Yes/No	Indication of delivery of OAT in PharmaNet
Receipt of prescriber safer supply (PSS) ^‡^	Yes/No	Concurrent PSS dispensations in PharmaNet.[70]

DIN: drug identification number

PIN: product identification number;

‡ Time dependent variable will be updated weekly;

a. ICD codes for each condition and DIN/PINs for different medications can be found elsewhere.[58]

**Table 5: T5:** Proposed subgroup and sensitivity analysis

Proposed sensitivity analysis	Rationale	Initiator/PP

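### Table 4 has no take-home supply item, so the per-protocol censoring weights leave out a time-varying factor that the plan itself flags

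*Protocol article*

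**What the plan says.** The Introduction, under the impact of COVID-19, lists what changed in several jurisdictions, Canada among them: "regulatory changes were implemented to expand take-home dosing, integrate telehealth consultations, and ease urine drug testing requirements". It adds: "While these adaptations largely applied to methadone and buprenorphine/naloxone, the impact on SROM accessibility and treatment outcomes remains unclear". Table 5 (Timeline restriction) names the same three changes, "such as increased take-home doses, expanded telehealth, and relaxed urine drug testing", and says that they "may have influenced treatment retention and outcomes". That is the reason given for the pre-COVID sensitivity analysis.

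Covariate selection states: "COVID-19-related covariates will be included to control potential selection bias introduced by pandemic-related service disruptions and differential treatment accessibility", and refers to Table 4 for the list. On use, it says: "These covariates will be used to estimate the inverse probability of treatment as well as censoring weights". The Initiator analysis section adds: "Same set of baseline and time-varying covariates will be included in the treatment and censoring models".

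Under COVID-19 related factors, Table 4 has virtual care, pharmacy delivery (defined as "Indication of delivery of OAT in PharmaNet") and prescriber safer supply. Under OAT experience it has urine drug testing in the past week. All four are updated weekly. No row covers take-home, carried or witnessed doses, or days supplied per dispensation.

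**The concern.** The per-protocol analyses censor people who switch, fall below a dosing benchmark, start a taper or stop meeting eligibility. They rely on the C2 and C3 weights to make those who remain stand in for those removed. This works only if the weight models contain the time-varying factors that predict both the censoring and the outcome.

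Take-home supply is a plausible factor of this kind. It tends to follow stability, and it sets how often a dispensation is recorded. Key measures asks for at least one qualifying dispensation per week. Read literally, a client holding more than a week's supply could have a week with no dispensing date and be censored under C3 for that reason alone. In the clone analyses, a client doing well enough to hold take-home doses may be less likely to switch to SROM by day 30, which would make the day-30 censoring of the switch clone informative.

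If the factor is left out and matters, the arm-specific risks and the SROM contrasts keep some of the selection bias that the COVID-19 covariates are meant to remove.

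**Working it through.** **1. Match each named change to Table 4.**

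| Change named in the Introduction and Table 5 | Item in Table 4 |
|---|---|
| Telehealth | Virtual care, weekly |
| Urine drug testing | Urine drug test in past week, weekly |
| Take-home dosing | None |

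Pharmacy delivery records how the drug arrives, not how many days are supplied. Safer supply is a separate product stream.

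**2. Look for other cover in the plan.**
- Calendar year is fixed at time zero, so it does not change when follow-up crosses March 2020.
- The pre-COVID restriction is a sensitivity analysis. It leaves the main estimates as they are, and the plan speaks of take-home dosing being expanded, so some existed before.
- High-dimensional propensity scores and instrumental variables are planned for the initiator analysis only.
- The limitations in the Discussion do not mention take-home dosing.

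**3. How much of the study lies in the affected period.** Inputs: accrual June 1, 2017 to December 31, 2022; cut-off March 17, 2020; follow-up capped at 24 months.
- Accrual window: 2,040 days, of which 1,021 run to the cut-off and 1,019 come after it (1,019/2,040 = 50.0%).
- Entries able to complete 24 months before the cut-off: those up to March 17, 2018, or 290 days (290/2,040 = 14%). The other 1,750/2,040 = 86% of entry dates have potential follow-up after it.
- With uniform entry and no early exit (assumption), about 61% of potential person-time falls after the cut-off.

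**4. Possible size.** The plan states no event rates, so there is no figure to reproduce and every rate below is an assumption. Take a weekly two-state model over 52 weeks. Let n0 and n1 be those without and with take-home doses, starting at n0 = 1 and n1 = 0. Discontinuation is d0 or d1 per week, C3 censoring is c0 or c1, and take-home doses are gained at rate g. Each week:
- h = (n0·d0 + n1·d1)/(n0 + n1), and S is multiplied by (1 − h);
- each n_k is multiplied by (1 − d_k)(1 − c_k);
- then g·n0 moves from n0 to n1.

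Risk is 1 − S at week 52. The truth has c0 = c1 = 0. The other rows show what is estimated when take-home status is ignored. Set d0 = 6%, with g = 3% on methadone and 1% on SROM. For methadone with d1 = 2%, week 1 gives h = 0.06 and week 2 gives h = 0.97 × 0.06 + 0.03 × 0.02 = 0.0588.

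| C3 per week, without / with take-home | d1 = 2%: methadone, SROM | Difference (error), points | d1 = 4%: difference (error), points |
|---|---|---|---|
| None (truth) | 0.851, 0.914 | 6.4 | 1.9 |
| 6% / 2% | 0.823, 0.885 | 6.2 (0.2) | 1.8 (0.1) |
| 10% / 2% | 0.802, 0.856 | 5.4 (1.0) | 1.5 (0.4) |
| 15% / 3% | 0.785, 0.832 | 4.6 (1.7) | 1.2 (0.7) |
| 3% / 15% | 0.929, 0.951 | 2.2 (4.2) | 0.8 (1.1) |
| Equal, e.g. 5% / 5% | 0.851, 0.914 | 6.4 (0) | 1.9 (0) |

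Errors are taken before rounding. With d1 = 2%, each arm's own risk moves by about 3 to 8 points: downwards when clients without take-home doses are censored more, upwards when they are censored less.

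**The case against.** **Strength of the factor.** A reader might infer that take-home supply is a main predictor of retention and overdose. The plan claims only a possible influence. The one study it cites on the subject, an Ontario survey, found no association between expanded unsupervised dosing and overdose, emergency visits or hospital admission. This stands.

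**Difference between arms.** A reader might also infer that take-home supply is known to be commoner on the comparators. The Introduction is describing policy across five countries, gives no BC rates by drug, and calls the effect on SROM unclear. An arm difference is a possibility, not a documented fact. This stands too.

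**Reach.** Key measures ties the primary outcomes to the initiator analysis, which has no C3 censoring and weights only for death and loss to follow-up. Dosing-benchmark censoring does not apply in (ix) and (x). This confines the point to the per-protocol and clone analyses.

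**Existing cover.** Virtual care, delivery, urine testing, calendar year and the pre-COVID restriction cover some of the gap. They are partial proxies, and none measures supply.

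**Size.** The model makes take-home status the only predictor and gives the proxies no credit, so it leans towards a larger bias. Even the direction of the dependence is open. This stands.

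**Feasibility.** The plan says that PharmaNet captures daily dispensations. It does not say that days supplied or a witnessed-dose flag is held. Nor can it be seen whether the cited covariate selection considered the variable and rejected it. The fix must allow for both.

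What remains is that the plan names three changes, gives controlling pandemic-related selection bias as the purpose of its COVID-19 covariates, and has an item for only two of the three.

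**Conclusion.** The gap is real and limited. The per-protocol censoring weights for (i)–(viii), and the switching and taper weights in the clone analyses of (ix)–(x), leave out a time-varying factor that the plan itself raises. The initiator analysis is little affected. The documents do not support calling take-home supply a dominant predictor, or saying that its distribution is known to differ by arm.

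Neither size nor direction can be derived from the documents. Under the assumed rates the risk difference is off by about 0.1 to 4 points at 52 weeks. The error is zero if censoring does not depend on take-home supply. The model covers discontinuation only; mortality and overdose visits were not modelled. The correction is worth making because it is specific and cheap, and the plan reports that no analysis has begun, so it can still be prespecified.

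**What to change.** 1. Add to Table 4 a weekly-updated take-home item derived from PharmaNet and lagged one week: for example, days supplied at the latest OAT dispensation, in bands.
2. Enter it in the denominator of the C2 and C3 censoring models, for the per-protocol analyses of (i)–(viii) and the clone analyses of (ix)–(x).
3. Amend the Initiator analysis sentence that puts the same covariates in both models, so that this item is excluded from the time-zero treatment model. Take-home supply arises after the drug is chosen and may depend on it.
4. State that weekly adherence is judged on days covered by a dispensation, not on dispensing dates. Otherwise a supply of 14 days or more would make C3 censoring near-certain in alternate weeks, which weighting cannot repair. Report the weight distribution with the new item included.
5. If PharmaNet cannot support the variable, list take-home dosing in the Discussion as an unmeasured time-varying confounder of the per-protocol analyses.

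Cost: one derived variable, a few lines of text and somewhat more variable weights. If PharmaNet supports the variable, no new data are needed.
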